### Methods in analysis to handle protocol non-adherence and any statistical methods to handle missing data {20c}

Outcomes will be assumed missing at random in the main analysis. We will perform one sensitivity analysis in which we impute missing outcomes using a chained equation approach, and another using the marginal structure model (MSM), which can handle possible bias introduced by noncompliance in the intervention group and informative censoring/dropout simultaneously.

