### Sample size {14}

A sample size of 3000 has >99% power to detect a difference in SPPB change as small as 0.54 points (the MCID) between the two groups at a two-sided alpha of 0.05, assuming a common SD of 2.7 for the SPPB change, 20% non-compliance, 10% dropouts, and an interim analysis. The estimates for MCID and SD are based on observation of older acute care medical patients [43, 44]. Using these same assumptions, the power is still 92% for detecting a smaller difference of 0.35. Therefore, we expect ample statistical power for analyzing the primary outcome. The main reason for selecting this sample size is to ensure that the analyses of important secondary outcomes are not underpowered. The most important of these is discharge disposition, because even a small absolute difference in the number of patients discharged to home, as opposed to a skilled nursing facility, is clinically important. We will be able to detect a 7% difference in discharge to home vs. SNF with 98% power.

For other binary secondary outcomes (a combination of venous thromboembolism, pneumonia and falls, 30-day mortality, or 30-day readmission), the study will have 85% power to detect a 33% reduction assuming an 8% rate in the control group. Because these outcomes are not contingent on patient cooperation, we anticipate no dropouts. For secondary continuous outcomes such as length of stay, assuming 20% non-compliance rate, the power to detect a 4-h difference (0.167 days) is 95%.

Regarding the cost analysis, there is no accepted way of doing a power calculation. However, we tried adding $300 (an approximation of the cost of the intervention) to the costs of each of 1500 patients drawn randomly from a sample of 3000 Cleveland Clinic medical inpatients over the age of 65 with an AM-PAC 6-Clicks score between 16 and 20. We then performed a *t*-test on the log-transformed costs, as described in the economic analysis section, and we were able to detect the increase with a p-value of 0.03, indicating that should the intervention increase costs by an amount equal to the cost of the intervention, we should be able to identify it. Similarly, if the intervention decreases total costs by $300 or more (not including the costs of the intervention), we should have sufficient power to detect it.

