## Statistical methods

### Statistical methods for primary and secondary outcomes {20a}

#### Statistical analyses

The main analysis will follow the intention-to-treat principle. The primary outcome, change in the SPPB from baseline to discharge (or 10 days), will be compared between the groups using an independent samples *t*-test. The large sample size should ensure that any confounding variables are equally distributed between groups. However, if we identify that any baseline variables are unbalanced and also associated with the outcome, we will model SPPB using a linear mixed-effects model to control for potential confounding. The fixed effects will include group, measurement time point, their interaction, site, and any unbalanced baseline variables. Secondary binary outcomes (discharge disposition and hospital-acquired complications) will be assessed using the chi-square test. The secondary longitudinal outcome (mobility improvement 30 days after hospital discharge) will be modeled using linear mixed-effects models.

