### Methods for additional analyses (e.g., subgroup analyses) {20b}

We will conduct three sensitivity analyses to account for (1) missing outcomes data, (2) treatment heterogeneity by site, and (3) the dose-response curve in the intervention group.

To identify the patients most likely to benefit from ambulating with a MT, we will build models separately for each treatment arm to predict the outcome of at least 1-point increase in the SPPB (i.e., beyond the minimal clinically important difference). Using the predicted probabilities resulting from these models, we will develop a Classification and Regression Tree (CART) that should identify subsets of patients likely to benefit, not benefit, or be harmed by the treatment. For example, the analysis might show that female patients aged >75 years who have an initial 6-Clicks score between 16 and 18 have an estimated treatment benefit of being 22% more likely to achieve the 1-point increase in SPPB. Essentially the tree will form risk groups of patients with shared characteristics that should receive a similar care recommendation.

We will estimate the total cost of the episode of care including the index admission (from hospital cost accounting systems) and all non-medication costs for the 30 days following enrollment (from Medicare claims) for all patients. For the intervention group, we will add the personnel costs for the MTs (hourly wages plus benefits). Since cost data are skewed, our cost estimates will be transformed and then compared between groups using the *t*-test.

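### The marginal structural model corrects for non-compliance and dropout together, so it estimates an adherence effect and cannot check the intention-to-treat result for dropout

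*Protocol article*

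**What the plan says.** Four places in the protocol article bear on this.

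- **Statistical analyses, under {20a}.** "The main analysis will follow the intention-to-treat principle". The change in SPPB score "will be compared between the groups using an independent samples" t-test.
- **Section {20c}, on non-adherence and missing data.** "Outcomes will be assumed missing at random in the main analysis". Two sensitivity analyses follow. For the first: "We will perform one sensitivity analysis in which we impute missing outcomes using a chained equation approach". The second is an MSM, "which can handle possible bias introduced by noncompliance in the intervention group and informative censoring/dropout simultaneously".
- **Section {20b}, additional analyses.** "We will conduct three sensitivity analyses to account for (1) missing outcomes data, (2) treatment heterogeneity by site, and (3) the dose-response curve". The third of these concerns intervention patients only. This list does not mention the MSM, and non-compliance is not among its purposes.
- **Sample size {14}.** The power statement for the primary outcome allows for "20% non-compliance, 10% dropouts, and an interim analysis".

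The article describes no version of the weighting analysis that handles dropout alone, and it does not label the MSM a supplementary or full-adherence estimate.

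**The concern.** Under intention to treat, a patient assigned to the mobility technician who walks little or not at all still counts in the effect being estimated. The question is what offering the service achieves, and incomplete uptake is part of the answer. An MSM that weights for compliance asks another question: what would be seen if assigned patients took up the intervention.

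A sensitivity analysis for missing data is informative when it keeps the target and varies only how missing outcomes are treated. The MSM as described changes both at once. If its estimate differs from the ITT estimate, the difference may come from the compliance weights, the censoring weights or both.

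This matters because the MSM is the only planned analysis that the article credits with handling informative dropout. The Discussion also accepts that the primary outcome may be missing for patients who go home without the team's knowledge. A reader of the results would naturally look to the MSM for reassurance on that point, and in its combined form it cannot give it.

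**Working it through.** **Inputs, from Sample size {14}:** 3,000 patients, so 1,500 per arm; SD of SPPB change 2.7; difference 0.54 points (the stated MCID) or 0.35; 20% non-compliance; 10% dropout; two-sided alpha 0.05.

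**Step 1. Reproduce the plan's power.** After 10% dropout there are 1,500 × 0.9 = 1,350 per arm.

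- SE = 2.7 × √(2/1350) = 0.104.
- Power ≈ Φ(difference/SE − 1.96).
- At 0.54 power is 99.9%, and at 0.35 it is 92.0%. Both match the article.
- If the 20% non-compliance dilutes 0.35 to 0.28, power is 76.9%.

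The stated 92% therefore reproduces only when the difference is read as the one observed between the randomised groups, with no further dilution. So it is not settled that 0.54 is the full-adherence effect, and Step 2 shows both readings.

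**Step 2. Gap between the two targets with no missing data.** Assume that non-compliers get no benefit. Then ITT effect = (1 − non-compliance) × full-adherence effect.

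| Reading | ITT effect | Full-adherence effect | Gap |
|---|---|---|---|
| 0.54 is the full-adherence effect | 0.54 × 0.8 = 0.432 | 0.54 | 0.108 |
| 0.54 is the ITT effect | 0.54 | 0.54 / 0.8 = 0.675 | 0.135 |
| 0.35 is the full-adherence effect | 0.35 × 0.8 = 0.28 | 0.35 | 0.07 |

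In every row the gap is 25% of the ITT effect (1/0.8 = 1.25). In the first row it is about one standard error (0.108 against 0.104).

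**Step 3. Vary the assumptions, taking 0.54 as the full-adherence effect.**

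- If non-compliers get half the benefit, ITT = 0.54 × (0.8 + 0.2 × 0.5) = 0.486 and the gap falls to 0.054.
- At the 70% adherence considered in the Discussion, again with no benefit in non-compliers, ITT = 0.54 × 0.7 = 0.378 and the gap is 0.162 (43%).
- The gap vanishes only if compliance makes no difference to the outcome.

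**Step 4. Simulation.** Settings: full-adherence effect 0.54, total SD about 2.7, and roughly 20% non-compliance and 10% dropout. Non-compliance depends on a prognostic covariate, as does dropout in the missing-at-random run. The covariate effects are assumptions. Each row is a separate draw, so small differences between rows are noise.

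| Missing data | ITT, observed cases | ITT, dropout weights only | MSM, both weights |
|---|---|---|---|
| None | 0.412 | 0.412 | 0.533 |
| Completely at random | 0.424 | 0.424 | 0.544 |
| At random given the covariate | 0.427 | 0.421 | 0.543 |

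The MSM exceeds ITT by about 0.12 in every row, including the row with nothing missing. Dropout weighting alone moves ITT by 0.006 at most. The MSM-to-ITT gap here reflects the compliance weights and says nothing about dropout.

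**The case against.** The strongest reply is that the article hides nothing. The heading of {20c} covers non-adherence as well as missing data, and the sentence states both roles of the MSM. The article also uses the term sensitivity analysis loosely: {20b} applies it to site heterogeneity and dose-response, and the dose-response curve within the intervention group does not estimate the ITT effect. Nowhere does it say that MSM-to-ITT agreement will be used to judge dropout. Missing data already have a cleaner check in the chained-equation imputation. How weights are built and results labelled can be left to a statistical analysis plan.

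Most of this stands, and it limits the point. It does not remove it. The article fixes that the two corrections are made simultaneously, and disclosing the combination does not make the result interpretable as a check on the ITT analysis. Imputation keeps the ITT target but normally also assumes missing at random.

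Three stronger readings are tempting, and the documents do not support them.

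- **That the plan calls non-compliance a bias of the main analysis.** The sentence speaks of possible bias from non-compliance in the intervention group and does not attach it to the ITT estimate.
- **That agreement between MSM and ITT could hide dropout bias.** Dropout bias would have to match the dilution of 0.108. At 10% dropout, the completer-minus-dropout gap in mean SPPB change would have to differ between arms by 0.108/0.10 = 1.08 points, or 0.4 SD. If the censoring weights removed that bias, imputation on the same variables would also expose it.
- **That missing data go unexamined.** The imputation analysis examines them separately.

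**Conclusion.** The point holds in a limited form. Because the MSM weights for compliance as well as dropout, it estimates an adherence effect, and its comparison with ITT cannot serve as a check on dropout.

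The illustrative gap is 0.108 points (0.54 against 0.432), or 25% of the ITT effect, before any outcome is missing. It rests on 0.54 being the full-adherence effect, 20% all-or-none non-compliance, and no benefit in non-compliers. The intervention is graded, with up to four visits a day and a goal of three walks, so partial compliers may well benefit and the real gap may be smaller.

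A reader might infer that the trial's main conclusion is at risk. It is not: the primary estimate, its test and the sample size do not depend on the MSM. What changes is which number can be offered as the second check on missing data.

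**What to change.** Make two changes in {20c}, and carry them into the statistical analysis plan if it does not already contain them:

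1. Run the weighting analysis with censoring weights only, in both arms, as the second missing-data sensitivity analysis on the ITT target. State that it relies on measured variables to explain dropout.
2. Report the model with compliance and censoring weights separately, as a supplementary estimate of the effect if the intervention were received. State that it is not a robustness check on the ITT result.

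The cost is some wording and one extra run of a model already planned. No new data are needed. The change is best made before outcome results by arm are seen.

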### Plans to give access to the full protocol, participant-level data, and statistical code {31c}

The investigators are committed to sharing the data from this study with the broader scientific community. As part of that effort, we will make our complete de-identified study data set, including study assignment, patient characteristics, and outcomes, available upon request from the Principal Investigator, 24 months after the conclusion of the randomized trial. Patient information will be de-identified in compliance with HIPAA regulations and requesters will be required to sign a data use agreement that prohibits them from attempting to reidentify participants. To the extent possible, case report forms for the study will be designed using Common Data Element conventions (https://www.nlm.nih.gov/cde/index.html) described in the subject areas of Demographics and Patient Contact Information, Medical History, and Study Details. All fields in the database will contain documentation to support the correct understanding of the data for internal and external data users.

## Oversight and monitoring

### Composition of the coordinating center and trial steering committee {5d}

The steering committee will meet monthly and be comprised of members of the study team, including experts in hospital medicine, physical therapy, nursing, organizational behavior, statistics, and health economics. There will be approximately 15 members. The committee will advise the PI on issues having to do with study design, decisions regarding implementation, data analysis, and interpretation. When the study is complete, the Steering Committee will oversee the publication of the manuscripts related to this work.

### Composition of the data monitoring committee, its role and reporting structure {21a}

The Data and Safety Monitoring Board (DSMB), composed of independent clinicians, will review the accumulating data with regard to recruitment, safety, and efficacy. The members of the DSMB will not be involved in the conduct of this study. The trial statisticians will summarize and report data to the DSMB semi-annually, and the DSMB will review the report and make recommendations to the investigators. Serious unexpected adverse events will be reported to the DSMB (and others) within 24 h of the study personnel learning of the events. NIA will recruit individuals to serve on the DSMB and schedule an initial meeting prior to starting the study. The purpose of the meeting will be to familiarize members with the protocol and to approve the DSMB charter, which will specify meeting frequency, data, and serious adverse event reporting requirements and stopping rules and guidelines.

### Adverse event reporting and harms {22}

We will monitor all adverse events and serious adverse events during the course of the study. Adverse events potentially related to the study will include any fall (defined as an event that results in a patient unintentionally coming to rest on the ground, floor, or other lower level), [47] which will be categorized as injurious or non-injurious; other musculoskeletal injuries; pulmonary embolism; and hospital-acquired infections. The principal investigator or his designee will assess each event for study-relatedness and severity. Serious adverse events will be reported to the Data Safety Monitoring Board (DSMB)

### Frequency and plans for auditing trial conduct {23}

The study coordinator at each site will audit the MT intervention logs and review step counts every month to ensure that participants are receiving the intervention, and they will provide feedback to the MT.

### Plans for communicating important protocol amendments to relevant parties (e.g., trial participants, ethical committees) {25}

Any protocol amendments deemed significant by the steering committee will be reviewed and approved by IRBs at both Cleveland Clinic and Baystate. These will also be shared with NIA.

## Dissemination plans {31a}

We plan to disseminate the results of the study widely and encourage their translation into practice in a number of ways, including through conference presentations (e.g., Society of Hospital Medicine and American Physical Therapy Association), peer-reviewed publications, and the creation of a Tool Kit. Embedded in the design of this project is the intent and plan to use the knowledge and products of the project to promote better care and minimize the harms of hospitalization for older adults. Results will be submitted to clinicaltrials.gov in a timely manner as specified by the NIH Policy on the Dissemination of NIH-Funded Clinical Trial Information.

### Local/regional dissemination

Members of the administration of our health systems are keenly interested in these results and would likely make these changes permanent if outcomes are favorable. Cleveland Clinic operates 15 hospitals in Northeast Ohio and Florida, while Baystate Health operates 4 hospitals in Western Massachusetts. Moreover, Cleveland Clinic is a national leader in healthcare innovation and holds annual meetings like the Innovation Summit. We will disseminate our findings at this meeting, and other similar meetings.

### National dissemination

To facilitate dissemination on a national scale, members of the study team will work with their respective professional societies, including the American Academy of Nursing, Gerontological Advanced Practice Nurses Association, Society for Hospital Medicine, American Physical Therapy Association, American Geriatrics Society, Association of Safe Patient Handling Professionals, and the American Society of Healthcare Risk Management (a subsidiary of the American Hospital Association) to promote the use of MTs through national guidelines and by influencing quality improvement organizations such as the Joint Commission and the National Quality Forum. Policy changes, including consensus guidelines and quality measures, are powerful catalysts for change at the health system level. By engaging appropriate thought leaders in national organizations, we will attempt to disseminate our findings through such policy changes. At the same time, we will work with various forms of media to disseminate our work. This will include the use of press releases to engage traditional media outlets and social media.

Finally, we will assemble a Tool Kit to facilitate the adoption of MTs by other health systems. The Tool Kit, which will be posted on the study website, will include materials necessary to start up a mobility tech program and carry out our intervention with high fidelity. It will include our MT training manual, instructions on how to license and use the 6-clicks instrument to determine patient eligibility, and will link to instructions on how to access and use the Johns Hopkins Mobility Goal Calculator. Study publications and links to other supporting articles will also be included.

## Discussion

In a 1947 issue of the British Medical Journal, Asher [63] advised against bed rest, writing: “Get people up and we may save our patients from an early grave.” Hirsch and colleagues [4] observed in 1990 that hospital-associated functional decline improved at a much slower rate than the acute illness. Such observations—now accumulated in multiple studies over more than 70 years—have led to labeling hospital-associated functional decline as an under-recognized epidemic [7] and identifying its role as part of the so-called post-hospital syndrome [64].

The primary objective of our study is to examine the extent to which ambulation interventions provided by an additional clinical team member—a MT—affects functional decline and other hospital-important outcomes (e.g., length of stay and discharge disposition) at costs that could be tenable for hospitals. Given current evidence, it is unclear if ambulation alone is enough to prevent the decline patients experience in the hospital. Further, we do not know how much ambulation may be required nor which patients benefit from ambulation, alone or in combination with other mobility interventions.

Appropriate exercise interventions in the hospital can, at the very least, attenuate functional decline. After cardiac surgery, ambulation facilitated by “ambulation orderlies” reduced functional decline and LOS [22, 37]. Kosse et al. [65] found in their systematic review that exercise interventions (provided by physical therapists or nurses) improved performance of physical function tests, contributed to fewer discharges to post-acute care facilities, and reduced hospital length of stay in a clinically heterogeneous sample of older adults. Similarly, in their single-center randomized controlled trial (*N*=370), Martinez-Velilla et al. [66] demonstrated that an individualized, multicomponent (resistance, balance, and basic mobility) exercise intervention in the hospital prevented functional decline and improved cognitive status.

Despite long-standing and ever-developing evidence that exercise could attenuate hospital-associated functional decline and lead to improved outcomes, physical activity interventions remain underutilized. This may be due, in part, to the relative complexity of these previously described interventions and the associated challenge of routinely implementing them in most hospitals. Additionally, usual care for hospitalized patients more often prioritizes fall prevention strategies that include bed rest—often with raised bedrails and activated bed alarms—over safe mobility practices [32]. With hospital quality metrics emphasizing fall prevention, [67, 68] and bedside nurses having multiple tasks that compete for their time and attention, [29] it is not surprising that patients only take, on average, 740 steps per day [33] and physician’s orders for ambulation are not completed up to 75% of the time [34, 69]. Indeed, nurses have reported concern about having limited time to provide mobility interventions, along with a lack of training and comfort with doing so [70].

Using MTs to assist with simple ambulation is consistent with the “culture of mobility” described as a goal for many hospitals, [71–73] in a way that does not further burden nurses. Early literature on the effects of in-hospital ambulation comes solely from observational or small prospective, randomized designs. One small nurse-led QI initiative demonstrated a 0.4-day decrease in LOS [70]. Another study noted that patients who walked more than 900 steps daily were less likely to experience functional decline (18% vs. 58%) [74]. A small randomized trial in the United States Veterans Health Administration (VHA) found that twice daily ambulation plus a behavioral strategy helped maintain post-hospitalization mobility [27]. An observational VHA study found that a daily walking program was associated with going home vs. a skilled nursing facility [18]. Our own prospective randomized controlled pilot trial in one hospital demonstrated that a MT could increase average daily steps from 668 to 994, with more intervention patients achieving 900 steps (28% vs. 19%). Additionally, intervention patients were more likely to go home [36]. No study, however, has used an experimental design to test the effect of MT-assisted ambulation on both in-hospital (including adverse complications) and post-hospital outcomes.

Our study will be the largest randomized controlled trial to test any exercise intervention for inpatients and tests a simple intervention (walking up to three times per day with a MT) that would be feasible for most hospitals to implement. There will be adequate statistical power to not only detect important differences in the primary outcome of mobility status, but also in less common hospital complications (falls, venous thromboembolism, pressure ulcers, and hospital-acquired pneumonia) that have been suspected to be due, at least in part, to unnecessary bed rest. We will also be able to develop a clinically useful classification model, allowing hospitals to recognize for whom ambulation with a MT may be most beneficial. This classification model will be strengthened by specific data on mobility dosing that we will collect from accelerometers. Lastly, our data will provide clear estimates of intervention costs relative to potential cost savings, information that will be important to help hospitals decide if implementation of a similar program is feasible for them.

Our study has limitations. First, the analyses of dose effect are observational and subject to confounding, as is the heterogeneity of treatment effect analysis to determine which patients benefit most. The cost analyses will suffer from some missing data. We may also have missing data for our primary outcome if patients go home without our knowing. Also, it is not clear whether the AM-PAC mobility measures can be reliably assessed by patient versus clinician raters at different time points without introducing measurement error [26, 75, 76].

Many potential limitations for our study are mitigated by the study’s design. For example, patients who are enrolled may be unable or unwilling to ambulate three times each day. If adherence is lower than expected in interim analyses, we will compare adherence rates across sites and attempt to identify and spread best practices. If that is not successful, we would still likely have sufficient power to detect a difference in our primary (>99% power with 70% adherence) and secondary outcomes (80% power with 70% adherence). Depending on the ease of enrollment, we may decide to enroll additional patients with the same resources. We anticipate heterogeneous patients, sites, and controls. Given our large sample, we anticipate that all of these important covariates will be balanced between the intervention and control arms. If we find that they are not, we will adjust our outcomes for important confounders. If we are unable to directly identify subgroups for whom the intervention is most beneficial, we will create a score, based on logistic regression, to identify patients who benefit if they score above a certain threshold. Alternatively, we will provide recommendations and tools to enable individual hospitals to incorporate our prediction model into the electronic health record and identify patients directly from the model.

While functional decline in the hospital is multifactorial, general out-of-bed mobility is a modifiable factor for many patients. This randomized controlled trial will test the effectiveness of MT-assisted ambulation on outcomes that matter to both patients and hospitals, including functional status, hospital discharge disposition, and the incidence of potentially avoidable hospital complications. It will also provide a useful estimation of cost implications to help hospital administrators assess the feasibility and utility of creating MT positions in their own hospitals.

